## Abstract

**Background:**

This paper describes a methodology for comparing the effects of an eduentertainment strategy involving a music concert, and a participatory class experience involving the description and making of a healthy breakfast, as educational vehicles for delivering obesity-preventing/cardiovascular health messages to children aged 7–8 years.

**Methods/design:**

This study will involve a cluster-randomised trial with blinded assessment. The study subjects will be children aged 7–8 years of both sexes attending public primary schools in the Madrid Region. The participating schools (n=30) will be randomly assigned to one of two groups: 1) Group MC, in which the children will attend a music concert that delivers obesity-preventing/cardiovascular health messages, or 2) Group HB, in which the children will attend a participatory class providing the same information but involving the description and making of a healthy breakfast. The main outcome measured will be the increase in the number of correct answers scored on a knowledge questionnaire and in an attitudes test administered before and after the above interventions*.* The secondary outcome recorded will be the reduction in BMI percentile among children deemed overweight/obese prior to the interventions. The required sample size (number of children) was calculated for a comparison of proportions with an α of 0.05 and a β of 0.20, assuming that the Group MC subjects would show values for the measured variables at least 10% higher than those recorded for the subjects of Group HB. Corrections were made for the design effect and assuming a loss to follow-up of 10%. The maximum sample size required will be 2107 children. Data will be analysed using summary measurements for each cluster, both for making estimates and for hypothesis testing. All analyses will be made on an intention-to-treat basis.

**Discussion:**

The intervention providing the best results could be recommended as part of health education for young schoolchildren.

**Trial registration:**

Clinicaltrials.gov: NCT01418872

## Background

Cardiovascular disease is the leading cause of death in the Western world [1]; indeed, in 2008 it was the cause of 31.8% of all deaths registered. In Spain, in that same year, ischaemic heart disease (IHD) was the most common cause of death among men (20,369 fatalities), while in women, stroke was the major cause of demise (18,312 deaths). The second cause of death among women was, again, IHD (15,519 fatalities) [2]. Numerous epidemiological studies have shown associations between different cardiovascular risk factors (CRF) and the appearance of these diseases and several of the classic CRFs (diabetes, obesity, high blood pressure and high cholesterol) are known to be influenced by poor dietary habits and the undertaking of little physical activity. These habits are hard to modify in adult life; it is therefore important to improve the development of lasting healthy habits during childhood [3,4].

Obesity is a CRF that has increased alarmingly in importance in recent years; indeed, the world is now faced with an obesity pandemic [5]. The World Health Organization (WHO) estimates there to be 1000 million overweight people worldwide, of which 300 million are obese [6]. Although the appearance of obesity is complex and influenced by genetic and other biological factors, poor diet and the undertaking of little physical inactivity are also involved. According to the National Health and Nutrition Examination Survey (NHANES) [7], obesity affects 17% of children and adolescents in the US. In fact, over the last 30 years the prevalence of obesity has nearly tripled in Australia, Brazil, Canada, the USA, Germany, France, Greece, the UK, and Japan (although it would now appear to be stabilizing in Sweden, the USA and the UK). In 2010, the prevalence of overweight/obesity was estimated at 40% for North America and the countries of the Eastern Mediterranean, at 38% for Europe, at 27% for the Western Pacific, and at 22% for Southeast Asia [8]. It is now known that overweight and obesity in childhood are associated with an increased risk of hypertension, diabetes, dyslipidemia and obesity in adulthood [9,10]. A number of studies from the USA (including the Bogalusa Heart Study) [11,12] and Finland [13,14] have shown that diseases that appear during older age may have their origin in earlier stages of life.

In Spain, the EnKid study showed the prevalence of overweight/obesity to be 30.4% among children aged 6–9 years (overweight alone = 14.5%, obesity alone = 15.9%) [15], while the Spanish National Health Survey showed 25.7% of girls and 29.3% of boys (aged 2–17 years) to be overweight/obese [16]. The International Obesity Taskforce (IOT) experts group reported the prevalence of childhood obesity in Spain to be among the highest in Europe [17], and in 2009, the Spanish system for the surveillance of risk factors associated with non-communicable diseases (SIVFRENT) highlighted the need to prioritise the surveillance of indicators related to energy balance given the increase observed in the prevalence of overweight/obesity, especially in girls [18]. Obesity, sedentary lifestyles, and poor nutritional and dietary habits are all increasing among the child population [19]. This age group should therefore be considered a priority for interventions aimed at promoting healthier lifestyles [20].

A review by the Cochrane Collaboration [21], in which 22 studies on improving either dietary habits or physical activity in children were analysed, concluded there to be insufficient data to affirm that the interventions undertaken helped prevent obesity. However, when changes were made to both the diet *and* physical activity, a small but positive effect on body mass index (BMI) was confirmed. However, other authors [22], who examined 158 studies mostly conducted in schools, emphasized the importance of exercise in achieving weight loss and preventing the appearance of chronic diseases in later life (note that some of these studies were reported to have problems in terms of their methodological quality).

In Spain, the Catalan Agency for Technology and Medical Research (AATRM) recently published a clinical practice guide for the prevention and treatment of childhood obesity [23]. This guide offers 64 evidence-based recommendations, 37 of which include the promotion of healthy eating habits and physical activity via educational programs that involve families and institutions. Spanish interventions aimed at preventing obesity take their inspiration in the home-grown PERSEO programme and the international NAOS strategy (Strategy for Nutrition, Physical Activity and Obesity Prevention) [24]. Both encourage information campaigns and agreements between public and private institutions in the health sector and beyond that could help goals be attained.

Townsend et al. reported that children make better food choices if schools promote healthy eating [25], and many studies have shown that inadequate breakfasts cannot be compensated for by other meals during the day [26-31].

One of the obesity prevention programmes promoted in schools is the “Healthy Breakfast Programme” [32]. This involves teaching primary schoolchildren the importance of having a good breakfast and of undertaking exercise. Public health workers, nurses and doctors at nearby health centres come to schools to teach – in the school dining room - that an adequate breakfast is important for all age groups, but especially for children. The Healthy Breakfast programme promotes 1) a breakfast consisting of a glass of full fat milk, two slice of bread with virgin olive oil, and a fruit (all key elements of the Mediterranean diet and representative of four food groups), and 2) physical activity through games in the playground. Primary school pupils usually aged 7–8 years receive a class on the importance of these points (see *Intervention Groups, Healthy Breakfast Group* below for a more detailed description), and take a reinforcing information pamphlet home. The programme has reached 37000 children over its 14 years of existence and has improved eating habits, e.g., the percentage of schoolchildren who have breakfast everyday has risen from 88% to 91.5% over this period [30]. Further, among those who already took breakfast, the composition of this meal has improved, with 84.4% now including four or more foods in this meal compared to a prior 77.4%. The motto of the campaign is “*First eat your breakfast, and then eat your day*” [32].

Music interventions have often been used to promote learning, communication and even to attain clinical goals [33-36]. In recent years, music has been used as part of cardiovascular health education. Williams et al. [37] showed that education via hip-hop music, used as a medium to deliver health messages to teenagers regarding strokes, reduced the time for assistance to be sought for adult stroke victims. In 2001, Marconato et al. [38] showed that including classical music in health education sessions reduced anxiety levels in students aged >18 years, increased personal happiness, promoted the consumption of fibre-rich foods, and reduced the intake of high cholesterol foods. Thus, music could be used to deliver educational messages in interventions aimed at promoting obesity prevention and the adoption of good cardiovascular health habits. In the present work, this music will be offered as an eduentertainment package [39], and will be provided by specialist musicians who have been involved in this type of project for some three years in the Madrid Region [40,41].

The proposed project aims to compare the effectiveness – in terms of knowledge and attitudes regarding obesity prevention/good cardiovascular health practices – of a health promotion strategy involving an Healthy Breakfast with that of an educational concert that delivers the same health messages via the vehicle of music and storytelling.

### Aims

The main aim of the proposed trial is to determine whether a health promotion strategy involving an educational music concert for schoolchildren aged 7–8 years improves knowledge of, and attitudes towards, obesity prevention/good cardiovascular health habits (as suggested by the NAOS strategy) better than a health promotion strategy involving an Healthy Breakfast.

The secondary aim is to compare the two interventions, at 6 months, in terms of the reduction achieved in BMI percentile by children who are overweight/obese prior to the start of the study.

## Methods

This study (ClinicalTrials.gov Identifier Number: NCT01418872) is a cluster-randomised clinical trial with parallel groups. A cluster design was chosen given the interest in performing the project in schools, and to prevent the contamination problems that would be faced if the children were the units of randomisation.

### Study population

Thirty public primary schools (clusters) will be selected among those that opt to be included in the proposed project (known as the Savinghearts Project) as one of the elective course offered by the Madrid Region education system. Thirty centres with at least two 2^nd^ grade classes (children’s ages 7–8 years) will be chosen by random sampling, stratified by rural/urban location and socioeconomic level. Each of the schools selected will be assigned a number and then randomised (using a random numbers table) to one of the intervention groups below (see *Intervention Groups*).

#### Inclusion criteria

Children must be present on the day of the planned activities, their parents or guardians must have given their informed consent for them to be included, and they should be subject to no exclusion criteria.

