#### Exclusion criteria

Children with food allergies or food intolerances, with uncorrected severe hearing impairment, whose parents do not give their informed consent, with a poor understanding of oral and written language, or who have previously been involved in the Healthy Breakfast Programme, will be excluded.

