#### Loss to follow-up

Withdrawals will be recorded when parents or tutors rescind consent for a pupil to continue. Few withdrawals may be expected since both proposed interventions are one-off experiences and are associated with no adverse effects. Further, the duration of the trial is only 6 months. Those children who do not complete the required questionnaires 7 days and 6 months after the interventions will also be considered lost to follow-up. Such problems can be minimised since the collaboration of the participating centres’ staff can be counted upon; indeed, the class teachers will be charged with passing out these questionnaires. Children will be weighed and measured on the day of the interventions and 6 months later. However, the nurse hired for the project will also go to the schools 3 days after the second measurement to measure those children who were not present, thus reducing loss to follow-up.

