### Statistical analysis

Primary analysis will be made on an intention-to-treat basis. The stages of the analysis will be:

1. *Descriptive analysis*. Quantitative variables will be described by their measures of central tendency, i.e., the mean or median (in the case of asymmetric distributions) plus the respective standard deviation or interquartile range. Qualitative variables will be described in terms of ratios.

2. *Comparison of the baseline characteristics of both groups*. The characteristics of the children in both trial arms, and of their families and their schools, will be described and compared. Special attention will be paid to variables that may influence the results. Parametric tests will be used to verify the effectiveness of randomisation. Potential confounders will be identified and appropriate adjustments made in the analysis of the primary efficacy variables.

3. *Primary efficacy analysis*. Relative risk, absolute risk reduction, and the relative reduction of risk will be used as measures of the strength of associations. The null hypothesis is that there are no differences between the two interventions in terms of improving the knowledge and skills associated with obesity prevention/good cardiovascular health habits. Multivariate analyses will be performed taking into account the type of design employed via the use of generalized linear models or multilevel models. The 95% confidence interval will be calculated for all estimates. A sensitivity analysis will be performed, assigning values supportive of the null hypothesis to all missing data.

All analyses will be made using PAWS and/or STATA software.

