### Ethical concerns

The described trial was evaluated and approved by the Central Committee of Primary Care Research in Madrid and the Clinical Research Ethics Committee of the Regional Community of Madrid. Information about the study, as well as its purpose and justification, will be provided to parents via the children’s school diaries. Parents/guardians will be asked to give their informed consent for their child to participate 10 days prior to the interventions; it will be collected by the class teacher from these same diaries. Consent is requested so that a child’s results can be assessed; no consent is required for the children to simply take part in the interventions since both fall within the official, free elective educational activities that can be chosen by the Madrid Region’s schools. A way for parents and class teachers to contact the principal investigator will be provided in order to resolve any queries that may arise.

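### Requiring presence on the day of the session excludes children after randomisation and contradicts the stated intention-to-treat analysis

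*Protocol article*

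**What the plan says.** Under Study population, the school is the unit of allocation: "Each of the schools selected will be assigned a number and then randomised (using a random numbers table") to the concert (MC) or the breakfast class (HB). The Inclusion criteria then set three conditions for the child: "Children must be present on the day of the planned activities", parental consent, and no exclusion criterion.

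The Statistical analysis section states: "Primary analysis will be made on an intention-to-treat basis". The abstract goes further and applies that principle to all analyses. The only stated provision for missing values is a sensitivity analysis that fills every missing value so as to favour the null hypothesis.

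Under Study stages and variables measured, the attitude baseline falls five school days before the session and the knowledge baseline the day before. Weight and height are first measured on the day of the session. The Loss to follow-up section counts withdrawal of consent and non-completion of the later questionnaires as loss. It does not mention absence from the session.

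**The concern.** Intention to treat in a cluster trial means that every eligible child of a randomised school is analysed in that school's arm, whatever the child then receives. A criterion that depends on attending the allocated session limits the analysis to children who were exposed. Two things are at stake:

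- **The question answered.** The trial would estimate the effect among attendees. A school or region deciding whether to offer one programme needs the effect among all the children to whom it is offered.
- **Comparability of the arms.** Randomisation of schools protects the comparison of all their eligible children. It does not protect a comparison of those left after a filter applied later, if absence differs between arms in amount or in the kind of child.

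**Working it through.** **Order of events for one child**

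1. Consent is sought 10 days before the session (Ethical concerns).
2. The attitude baseline is taken five school days before (Study stages and variables measured). Assessment of efficacy says seven days; the order is the same either way.
3. The knowledge baseline is taken one day before.
4. On the day, the session is held, first weight and height are measured, and the presence criterion is met or failed.
5. Knowledge is tested again at 7 days and 6 months, and attitudes at 6 months.

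The article does not date randomisation relative to steps 1 to 3. It must precede step 4, because the content of the session is the allocation. So the presence criterion is decided after randomisation and after both baselines for the main outcomes.

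**A child who completes steps 1 to 3 and is absent at step 4**

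- Under the Inclusion criteria, the child is not included.
- Under intention to treat, the child belongs in the school's arm.
- Under Loss to follow-up, the child is not lost, since absence from the session is not a listed reason.
- Under the sensitivity analysis, the child receives no imputed value, since that analysis acts on missing data of included children.

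The first two statements cannot both be followed, and neither of the other provisions resolves the conflict.

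**Size of bias: illustration only**

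All exclusion rates here are assumed. Take no true difference, with success 40% in both arms (40% is the HB figure in the Sample size section). If a share *e* of an arm is excluded and those children would succeed with probability *q*, the rate among the rest is (0.40 − *e* × *q*) / (1 − *e*).

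| *q* | *e* = 5% | *e* = 10% | *e* = 15% |
|---|---|---|---|
| 0.20 | 0.390/0.95 = 41.05% | 0.380/0.90 = 42.22% | 0.370/0.85 = 43.53% |
| 0.30 | 0.385/0.95 = 40.53% | 0.370/0.90 = 41.11% | 0.355/0.85 = 41.76% |

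With 5% excluded in one arm and 10 to 15% in the other, the spurious difference runs from 0.6 points (*q* = 0.30, 5% v 10%) to 2.5 points (*q* = 0.20, 5% v 15%). The planned difference is 50% − 40% = 10 points. With equal *e* and *q* in both arms it is 0.

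**Cost of keeping absentees**

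Suppose a share *a* is absent in both arms and absentees show no difference between arms. The 10-point contrast becomes 10 × (1 − *a*). For an assumed *a* of 3 to 8%, that is 9.7 to 9.2 points.

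**The case against.** The strongest reply is that little is lost in practice. Nothing moves a child out of the school's arm, so this is not an as-treated analysis; at most it is a modified intention-to-treat set. Both arms offer a one-hour session in school hours with the same messages and take-home items, and absence from a single school day has no evident link to the arm. Outcome markers are blinded. All of this stands, and it is why the bias is likely modest. It does not remove the contradiction: the stated principle and the stated criterion define different analysis sets.

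A reader might also infer three stronger points. The article does not establish them.

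- **Enrolment by people who know the arm.** "Parents/guardians will be asked to give their informed consent for their child to participate 10 days prior to the interventions", and "it will be collected by the class teacher from these same diaries". No blinding of parents or teachers is stated. But the article says neither whether consent precedes randomisation nor when schools learn their arm. Consent also governs only the use of data ("Consent is requested so that a child’s results can be assessed"), so a parent cannot gain or avoid a session by giving or refusing it. Even if consent did follow allocation, that would be a recruitment-bias risk and not a breach of intention to treat.
- **Exclusions applied differently by arm.** "Children with food allergies or food intolerances, with uncorrected severe hearing impairment" bear unequally on a meal and a concert, but they stand in one list for all children. Nothing says that they are sought differently in the two arms.
- **Selection by questionnaire completion.** "Those children who do not complete the required questionnaires 7 days and 6 months after the interventions will also be considered lost to follow-up". That is loss to follow-up, not ineligibility, and the sensitivity analysis covers missing data. Recent acquisition and later memory of knowledge are separate outcomes, and nothing says that one missing form discards the other.

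**Conclusion.** The point holds for the presence criterion alone. As written, it excludes consented, eligible, baseline-tested children of randomised schools, in contradiction of the declared intention-to-treat analysis, and the missing-data analysis does not bring them back. This rests on reading the planned activities as the intervention session, which is the natural sense, since the article uses that word for the breakfast session and sets no other single day.

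The size of any bias cannot be derived from the article. The 0.6 to 2.5 points above require unequal exclusion between arms and excluded children who would score worse than the rest, and the article supports neither. Consent timing, the exclusion list and questionnaire completion are risks worth monitoring; they should not be presented as contradictions of intention to treat.

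**What to change.** - Delete presence on the day from the inclusion criteria.
- Define the intention-to-treat set as all eligible, consented children in randomised schools, analysed in their school's arm whether or not they attended.
- Keep attendees as a supportive set.
- Report non-consent, exclusions and absence on the day by arm, so that readers can judge whether selection differed.
- State a rule for the BMI outcome. Absentees will have no weight and height from the session day, and the nurse's return visit is described only for the 6-month measurement. They should be measured on another day close to the session, or be treated as missing for that outcome.

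The cost is small. Class teachers already hand out the follow-up questionnaires, so absentees can be followed by the same route. The contrast is slightly diluted, as shown above. Withholding the allocation until after the baseline tests is not part of this fix. The knowledge test is the day before the session, which would leave one day to arrange the hall, food or musicians unless testing were moved.
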